### Aims

This protocol describes the study design and methodology of the MINISTOP 2.0 trial, using a hybrid type 1 effectiveness-implementation study design. The overall aim of the MINISTOP 2.0 trial is to evaluate whether an mHealth intervention, embedded in the routine services of primary child health care in Sweden, can be used to promote healthy dietary and activity behaviours and to decrease the prevalence of overweight and obesity in preschool-aged children. Specifically, we aim to evaluate:
The effectiveness of the MINISTOP 2.0 app in terms of effects on: a) key dietary indicators, assessed as intake of fruit and vegetables, sweet and savoury treats and sweet drinks (primary outcome); b) physical activity, assessed as time spent on moderate-to-vigorous physical activity (primary outcome); c) screen time (primary outcome); d) body mass index (BMI) (secondary outcome); and e) parental self-efficacy (secondary outcome).The implementation of the MINISTOP 2.0 app with regard to perceived acceptability, appropriateness, and feasibility among parents and primary health care nurses.

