#### Outcome measures

The primary outcomes for the effectiveness of the intervention are diet, physical activity and screen time. BMI and parental self-efficacy are secondary outcomes. Outcomes are assessed at baseline and at 6-months’ follow-up at the primary child health care centres. See Fig. 2 for an overview of all assessments, Fig. 3 for participant timeline and Supplementary material to see all questions used for outcome measures.

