#### Data analysis

All analyses will be intention-to-treat, including participants in the groups to which they were randomly allocated. Analyses will first be among complete cases, assuming that any missing data are missing completely at random (MCAR). Attrition and sensitivity analyses will be conducted to assess the plausibility of the MCAR assumption and the effect of potential outliers on the analytical results (Supplementary material). Data input will be checked against source data to ensure that translation from paper questionnaires to digital format did not introduce errors.

Parameters of all models will be estimated using maximum likelihood (MLE) and Bayesian inference [45]. Null hypothesis testing will be conducted at the conventional 0.05 significance threshold. Marginal posterior distributions for coefficients of interest will be examined to calculate the posterior probability of effect (i.e. the proportion of parameters compatible with the MINISTOP 2.0 intervention having a positive effect). The median of the marginal posterior distributions will be used as point estimates of effect. Both null hypothesis testing and Bayesian analysis will create a basis for scientific inference.

Primary outcomes comprising intake of fruit and vegetables, sweet or savoury treats or sugar-sweetened drinks, average minutes per day of moderate-to-vigorous physical activity, and average time spent in front of digital screens (TV, computer, iPad/tablets or mobile phones) will be analysed using normal regression (possibly log transformed if found to be skewed). The secondary outcome of BMI will be analysed using quantile regression (at 10, 50, and 90% quantiles). Furthermore, the secondary outcome of self-efficacy will be analysed using normal regression (possibly log transformed if found to be skewed). All models will include a random intercept accounting for differences among child health care centres, a regressor for group allocation to determine contrasts in the intervention and control groups, adjustment for the baseline value of each respective outcome, and adjustments for age and gender of the child. Effect modification will be analysed by introducing an interaction term between group allocation and baseline variables.

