#### Sample size

With 360 participants (180 per group) completing follow-up, a mere 0.30 standard deviation (SD) difference in outcomes between groups with a power of 80% (α = 0.05) can be detected. This corresponds to differences of 25 g and 0.4 kg/m^2^ in fruit intake and BMI, respectively [23, 28]. We will conduct interaction analyses to examine whether the effect of the intervention differs depending on socioeconomic and migration status. Assuming a maximum dropout rate of ≈ 25–30% [23, 28], 500 children will be recruited. This sample size is considered feasible given our own and other researchers’ previous experiences [23, 28].

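### Five unranked primary outcomes share one 0.05 threshold with no multiplicity control or success rule, so a single significant result could be read as effectiveness at up to about 23% error (about 12% for false benefit)

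*Protocol article*

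**What the plan says.** The Aims section labels each behavioural target as primary:

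- Diet, as three indicators: "key dietary indicators, assessed as intake of fruit and vegetables, sweet and savoury treats and sweet drinks (primary outcome".
- Physical activity: "physical activity, assessed as time spent on moderate-to-vigorous physical activity (primary outcome".
- Screen time: "screen time (primary outcome".

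The Data analysis section of the effectiveness evaluation lists the same five measures as primary outcomes, to be analysed by normal regression. The Outcome measures section counts differently: "The primary outcomes for the effectiveness of the intervention are diet, physical activity and screen time". That is three domains.

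One error level is given for all models: "Null hypothesis testing will be conducted at the conventional 0.05 significance threshold". Data analysis makes exploratory only those measures that are neither primary nor secondary. It also says: "Both null hypothesis testing and Bayesian analysis will create a basis for scientific inference". The article gives no posterior cut-off.

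The Sample size section takes 180 completers per group and 0.30 SD, and states that such a "difference in outcomes between groups with a power of 80% (α = 0.05) can be detected". The article mentions no multiplicity adjustment, hierarchy, composite or all-must-succeed rule.

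**The concern.** The abstract makes national implementation conditional on proven effectiveness, together with acceptability, appropriateness and feasibility. The article does not say what pattern of results across five primary outcomes would count as proof. With five measures of equal standing and one unadjusted threshold, a reader or the authors could take a single p-value below 0.05 as a positive trial. The error rate of that reading is well above the stated 0.05.

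The measures are parent-reported and unblinded. The Discussion accepts that this raises the risk of differential social desirability bias, which makes a loose evidential standard less comfortable. The predecessor trial, as described in the Background, reported one composite score of six behaviours. No composite is defined here.

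**Working it through.** **Inputs from the protocol.** Five primary measures (Aims; Data analysis) or three domains (Outcome measures); α = 0.05; 180 completers per group; 0.30 SD; 80% power. Sidedness is not stated. The correlation among outcomes and the baseline–follow-up correlation are not given, so ranges are assumed below.

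**Reproducing the stated sample size.** For a two-sided test, n per group = 2(1.960 + 0.842)²/0.30² = 174.4, so 175. A one-sided test would need 138, so two-sided fits the stated 180. Power with 180 per group at 0.30 SD is 81%. The stated figure is right for one comparison at 0.05.

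**Family-wise error if any single significant result counts.** With m independent tests, the chance of at least one false positive is 1 − 0.95^m in either direction. It is 1 − 0.975^m in the beneficial direction only.

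- m = 5: 1 − 0.95^5 = 22.6%; beneficial direction 1 − 0.975^5 = 11.9%.
- m = 3: 1 − 0.95^3 = 14.3%; beneficial direction 1 − 0.975^3 = 7.3%.

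All five measures come from one parent questionnaire, so positive correlation is plausible. Simulating five equally correlated normal test statistics (1,000,000 replicates) gives:

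| Assumed correlation | Either direction | Beneficial direction only |
|---|---|---|
| 0 | 22.6% | 11.9% |
| 0.3 | 21% | about 10.5% |
| 0.5 | 18% | about 9% |
| One test, for comparison | 5% | 2.5% |

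**Power at the adjusted level.** The first Holm step for five outcomes is 0.05/5 = 0.01. Under the stated rule, the chance of any false rejection in the beneficial direction is then at most 5 × 0.005 = 2.5%. Power per outcome comes from the noncentral t distribution with 180 per group. With baseline adjustment, the standardised effect becomes 0.30/√(1 − r²), where r is the assumed baseline–follow-up correlation.

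| Analysis | Effect (SD) | Power at 0.05 | Power at 0.01 |
|---|---|---|---|
| No baseline adjustment | 0.300 | 81% | 60% |
| r = 0.4 | 0.327 | 87% | 70% |
| r = 0.5 | 0.346 | 91% | 76% |
| r = 0.6 | 0.375 | 94% | 83% |

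Without baseline adjustment, the difference detectable with 80% power at 0.01 is (2.576 + 0.842) × √(2/180) = 0.36 SD, against 0.295 SD at 0.05.

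**Power for at least one rejection at 0.01, without baseline adjustment.** With 0.30 SD on three of the five outcomes, it is 94%, 88% and 84% at assumed correlation 0, 0.3 and 0.5. With an effect on one outcome only, it is about 61%.

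**The case against.** Several objections have force.

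- **Direction and independence.** The 22.6% counts significant harm as well as benefit and assumes independent outcomes. A reader might infer that the chance of a false claim of effectiveness is 23%. The documents do not support that: a false claim of benefit is at most about 12% under independence or positive correlation. This stands.
- **Success rule.** The article nowhere says that one significant result out of five is enough. It does not exclude it either. The error rates are therefore conditional on that reading, and the missing rule is part of the point.
- **Bayesian analysis.** A reader might take the posterior probability as a second, unprotected route to a claim that adds to the error. The text can equally be read as describing one joint basis for inference, and it gives no cut-off. With a vague prior and a 0.975 cut-off (both assumptions), the posterior criterion is the same event as one-sided p < 0.025 and adds nothing. None of the 23% comes from this source.
- **Left to the analysis plan, or separate claims.** A multiplicity procedure often sits in an analysis plan, which is not shown. Unadjusted tests can also be defended if each outcome supports only its own claim, as the lettered list in Aims might suggest. This softens the point but does not remove it. The article itself fixes 0.05, bases its power on 0.05, and keeps all five measures outside the exploratory category. A later adjustment would alter both the threshold and the power stated here.

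**Conclusion.** The point holds in this form: five unranked primary outcomes share one 0.05 threshold, and the article states no multiplicity control, hierarchy or success rule. It also counts the primary outcomes in two ways.

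The size depends on an assumption the article leaves open, that any single significant result would be taken as effectiveness. On that assumption the family-wise error is up to about 23% in either direction and up to about 12% for false benefit. Even the count of three domains gives about 14% in either direction under independence. The sample-size calculation is correct for a single comparison, but it does not describe a trial that controls error over five.

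**What to change.** 1. In Outcome measures and Data analysis, list the same five primary outcomes, so that the testing family is fixed.
2. Control the family-wise error at two-sided 0.05 with Holm, or with a fixed testing order stated in advance.
3. Define success as at least one adjusted rejection in the beneficial direction.
4. State that posterior probabilities describe the same estimates and are not a separate route to a claim.
5. Restate the Sample size section at the adjusted level: power per outcome at 0.01, with and without baseline adjustment and with the assumed correlation given, and the detectable difference of about 0.36 SD without adjustment.

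The cost is wording, plus a less favourable stated power for each outcome. Like for like, that is 81% to 60% without baseline adjustment, or 87/91/94% to 70/76/83% at assumed correlations of 0.4/0.5/0.6. Power for at least one rejection is higher if several outcomes improve, as shown above. A fixed order would keep the full 0.05 for the first outcome, but a failure there would stop formal testing of the rest. The Trial status section says the protocol was finalised before the research team had received any data, and the article already provides for reporting important modifications in the registration and the results papers.

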### Intervention effectiveness evaluation

The MINISTOP 2.0 trial is a two-arm parallel group randomised controlled trial. In total, 500 children aged 2.5–3 years are being recruited during their routine visit at primary child health care in ≥15–20 health care centres throughout Sweden, covering various socioeconomic areas. Following baseline assessment, parents are randomised (1:1) to the intervention (MINISTOP 2.0 app + standard care) or control group (standard care). Outcome measures will be assessed 6 months post randomisation at a routine visit to child health care.

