#### Participants and recruitment

All children who attend the routine visit at 2.5–3 years in primary child health care will be screened for eligibility to participate. To be included, at least one parent must be able to speak and read Swedish, English, Arabic or Somali sufficiently to understand consent information. In addition, the Somali and Arabic versions of the app contain audio-files, to facilitate reading and ensure that parents with limited reading skills can also benefit from the content of the app. The nurses were instructed not to offer trial participation to families where the child is diagnosed with a neurological or endocrine disease or where a parent is suffering from a serious physical or mental illness, which would make the trial too demanding for the family.

Information about the trial is sent to the families’ home addresses together with a routine invitation to visit the primary child health care centre when the child is aged 2.5–3 years. A child health care nurse will ask families about participation in the trial and collect written informed consent from parents. Thereafter, parents complete a questionnaire about the child’s diet, physical activity, screen time, physical fitness and dental health behaviours. The parents also answer questions about their own socioeconomic background as well as questions on parental self-efficacy regarding their own ability for promoting healthy physical activity and dietary behaviours in their child. The nurse also measures the child’s height and weight in a standardised way. Subsequently, participating families are randomised to either an intervention or control group using opaque envelopes. Participants in the intervention group are given access to the MINISTOP 2.0 app for 6 months, in addition to standard care, while those in the control group only receive age-appropriate information about healthy food and physical activity that currently is provided by routine child health care. Six months after randomisation families will attend another routine visit at the primary child health care centre. The nurse again measures the child’s weight and height and the parents complete the same questionnaire about the child’s food, physical activity, screen time, fitness and dental health behaviours. At this visit, the control group will also be offered access to the MINISTOP 2.0 app. Figure 2 outlines the study design and Fig. 3 presents a trial participant timeline.

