##### Health behaviours

The MINISTOP 1.0 app has previously been evaluated with accurate and valid methodology for assessment of body composition, dietary intake and physical activity [28]. In the MINISTOP 2.0 trial, we used a short questionnaire for the outcome measures as all measures are performed by the health care nurses and therefore need to be easily administered. Thus, the questionnaire addresses questions to the parents about their children’s diet, physical activity and screen time. Diet and physical activity are assessed using a modified version of the National Board of Health and Welfare’s survey of health behaviours [40]. Key dietary indicators, i.e. fruit and vegetables, sweet or savoury treats or sugar-sweetened drinks, will be assessed as average number of standardised portions per day during the past month. Physical activity will be assessed as average minutes per day of moderate-to-vigorous physical activity in the past month. Average time spent in front of digital screens (TV, computer, tablets or mobile phones) will be assessed in minutes per day during a typical week and weekend (the past month) based on a questionnaire with established reliability [41]. The questionnaire also contains questions about the child’s dental health behaviours and physical fitness [42]. Finally, the questionnaire addresses questions to the parents about their own age, height and weight, education, country of birth and self-efficacy for promoting healthy physical activity and dietary behaviours in their child [28, 43].

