### Trial status

Recruitment of participants to the MINISTOP 2.0 trial was initiated in November 2019 and the trial is progressing according to plan. This protocol was finalised before the research team had received any data.

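### The stated models carry no calendar term although the two visits fall half a year apart, so precision is lost on season-sensitive outcomes; a cheap, low-severity improvement

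*Protocol article*

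**What the plan says.** All references are to the protocol article.

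- **Timing.** Under Intervention effectiveness evaluation: "Outcome measures will be assessed 6 months post randomisation at a routine visit to child health care". Participants and recruitment repeats this: "Six months after randomisation families will attend another routine visit at the primary child health care centre". Randomisation follows directly on the baseline measures.
- **Recall window.** Under Health behaviours, activity is recorded as "average minutes per day of moderate-to-vigorous physical activity in the past month" and screen time as "minutes per day during a typical week and weekend (the past month"). The dietary portions also refer to the past month.
- **Model.** Under Data analysis: "All models will include a random intercept accounting for differences among child health care centres", together with a group term, "adjustment for the baseline value of each respective outcome, and adjustments for age and gender of the child". No season, month or calendar-time term is named anywhere.
- **Calendar.** Under Trial status: "Recruitment of participants to the MINISTOP 2.0 trial was initiated in November 2019". The length of the recruitment window is not given.
- **Allocation.** Randomisation and blinding gives a 1:1 ratio, random blocks of 2 and 4, and sealed envelopes. It does not say whether lists were central or per centre, or in what order envelopes were drawn.

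**The concern.** A past-month report carries the season in which it is made. With a planned gap of half a year, a child with a winter baseline has a summer follow-up, and the reverse. For an outcome with a yearly cycle this is the least favourable gap for baseline adjustment. The seasonal part is positive at one visit and negative at the other, so it adds variance at follow-up and also pulls down the baseline–follow-up correlation. At a twelve-month gap it would have the same sign at both visits.

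None of the listed covariates stands in for calendar date. Child age is not date, and the centre intercept picks up season only if centres recruit at different times of year. At stake is the width of the intervals on the primary outcomes that season plausibly touches, chiefly physical activity and screen time. The same precision feeds the planned interactions with socioeconomic and migration status, for which no separate power is given.

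**Working it through.** **1. The plan's own figure.** Sample size: 180 completers per arm, 0.30 SD, 80% power, α = 0.05 (two-sided assumed).

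- Needed per arm: 2 × (1.960 + 0.842)² / 0.30² = 174.4, so 175.
- Power at 180 per arm: Φ(0.30 / √(2/180) − 1.96) = Φ(0.886) = 81.2%.
- Recruitment: 500 × (1 − 0.28) = 360.

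The figure reproduces. It is an unadjusted two-sample calculation and takes no credit for baseline adjustment.

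**2. Assumptions, none of them in the article.** Season is a yearly sine wave explaining a share f of total outcome variance (total variance set to 1). The within-season baseline–follow-up correlation is ρ. Entry is spread evenly over a full year.

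**3. Formulas.**

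- Observed correlation: c = ρ(1 − f) − f. The final −f is the opposite-sign seasonal part.
- Residual variance, stated model: 1 − c².
- Residual variance with season terms: (1 − f)(1 − ρ²).
- Power: Φ(0.30 / √(2 × residual variance / 180) − 1.96).

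**4. Results at ρ = 0.5.**

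| f | c | Residual variance, stated model | With season terms | Ratio | Cut in SE (1 − √ratio) | Power, stated → with season |
|---|---|---|---|---|---|---|
| 2% | 0.470 | 0.779 | 0.735 | 0.943 | 3% | 89.7% → 91.3% |
| 5% | 0.425 | 0.819 | 0.713 | 0.870 | 7% | 88.2% → 92.1% |
| 10% | 0.350 | 0.878 | 0.675 | 0.769 | 12% | 86.0% → 93.4% |

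The power gains are 1.6, 3.9 and 7.4 percentage points.

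**5. Sensitivity to ρ and amplitude.** An independent calculation used the amplitude A of the wave in within-season SDs, where f = (A²/2) / (1 + A²/2); A = 0.3 is f of about 4%. With year-round entry, the stated-model SE divided by the SE with season terms is:

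| ρ | A = 0.1 | A = 0.5 |
|---|---|---|
| 0.3 | 1.005 | 1.098 |
| 0.5 | 1.007 | 1.155 |
| 0.7 | 1.014 | 1.277 |

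At A of 0.1–0.2 the inflation is only about 0.5–5%.

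**6. Sensitivity to recruitment length.** Simulation with 360 children, 18 centres, ρ = 0.5 and A of 0.2, 0.3 or 0.5 gave these SE ratios:

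- 3-month entry: 1.001, 1.002, 1.007.
- 6-month entry: 1.011, 1.026, 1.067.
- 12-month entry: 1.029, 1.062, 1.155.

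The effect estimate was unbiased throughout.

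**7. Calibration of the intervals.** Null rejection of the stated model at nominal 5%, 3,000 simulated trials, 12-month entry:

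| f | Blocks used in time order | Allocation unrelated to time |
|---|---|---|
| 2% | 0.046 | 0.052 |
| 5% | 0.038 | 0.048 |
| 10% | 0.035 | 0.053 |

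With season terms and time-ordered blocks the rates return to 0.047–0.048. Simulated power in that setting goes from 0.898, 0.901 and 0.876 to 0.910, 0.923 and 0.927. These gains of 1, 2 and 5 points are smaller than in step 4, because time-ordered blocks already take part of the seasonal variance out of the estimate.

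**The case against.** The strongest reply is that nothing here is invalid. Analysis of covariance with baseline, age, gender and centre is a sound model without a season term, many other prognostic covariates could be proposed, and the article does not say that its list is exhaustive. Every size above also rests on quantities that the article does not give. Most of this stands, and it sets the severity. What remains is that the article does state a covariate list for all models, and the six-month gap makes this one omission costlier than most.

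A reader might infer four stronger things that the article does not support.

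- **Bias.** Both arms pass through the same seasons under concurrent 1:1 allocation, and the simulated estimates are unbiased.
- **An underpowered trial.** The 80% comes from an unadjusted calculation. For 0.30 of the outcome SD, the stated model stays at 82% or above in every scenario computed. It falls below 80% only if the 0.30 is rescaled to the smaller within-season SD (77.5% at ρ = 0.3, A = 0.5), which is not how the article states the effect.
- **Intervals that are too wide in themselves.** That holds only if envelopes were used in time order and season is fairly strong. Otherwise coverage is nominal, and the only loss is relative to a better model.
- **A loss equal to 30% more children.** At f = 10% the ratio of reported variances is 1/0.769 = 1.30, but under time-ordered blocks the true loss is smaller. At ρ = 0.5 and A = 0.5 the model SE is 0.105, the actual sampling SE 0.097, and the model SE with season terms 0.091. The variance gap is then (0.097/0.091)² = 1.14, not (0.105/0.091)² = 1.33.

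No seasonal argument has been made for the BMI quantiles or for parental self-efficacy.

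**Conclusion.** The point holds as a cheap improvement of low severity. The six-month gap, the past-month recall and the covariate list are all in the article, and the direction follows from them: any yearly seasonal component inflates the residual variance and weakens the baseline adjustment.

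The size is conditional. At a correlation of 0.5 with year-round entry, the standard error could be cut by about 3%, 7% or 12% for a seasonal share of 2%, 5% or 10%. It becomes material from an amplitude of about 0.3 within-season SD with entry over most of a year, and is negligible with entry over about three months. If envelopes were drawn in time order, tests are also mildly conservative at 5–10% season, rejecting a true null about 3–4% of the time instead of 5%.

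**What to change.** Pre-specify in the primary-outcome models either a sine and a cosine term of the baseline visit (or randomisation) date, or calendar-quarter indicators. Physical activity and screen time are the main candidates; diet is optional. BMI quantiles and self-efficacy do not need them. Use the baseline date, which is fixed before allocation, rather than the actual follow-up date, so that late visits do not bring a post-randomisation variable into the model.

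The cost is one sentence in the analysis section and two or three coefficients in about 360 children. The article does not say that the date is recorded, but a follow-up timed from randomisation needs it. If seasonality is weak or recruitment short, little is gained and little is lost. The terms should be fixed before outcome data are seen, since adding them later would look data-driven.
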